## Abstract

**Background:**

Because of symptoms, people with lumbar spinal stenosis (LSS) are often inactive, and this sedentary behaviour implies risk for diseases including obesity. Research has identified body mass index as the most powerful predictor of function in LSS. This suggests that function may be improved by targeting weight as a modifiable factor. An e-health lifestyle intervention was developed aimed at reducing fat mass and increasing physical activity in people with LSS. The main components of this intervention include pedometer-based physical activity promotion and nutrition education.

**Methods/Design:**

The Spinal Stenosis Pedometer and Nutrition Lifestyle Intervention (SSPANLI) was developed and piloted with 10 individuals. The protocol for a randomized controlled trail comparing the SSPANLI intervention to usual non-surgical care follows. One hundred six (106) overweight or obese individuals with LSS will be recruited. Baseline and follow-up testing includes dual energy x-ray absorptiometry, blood draw, 3-day food record, 7-day accelerometry, questionnaire, maximal oxygen consumption, neurological exam, balance testing and a Self-Paced Walking Test. Intervention: During Week 1, the intervention group will receive a pedometer, and a personalized consultation with both a Dietitian and an exercise specialist. For 12 weeks participants will log on to the e-health website to access personal step goals, walking maps, nutrition videos, and motivational quotes. Participants will also have access to in-person Coffee Talk meetings every 3 weeks, and meet with the Dietitian and exercise specialist at week 6. The control group will proceed with usual care for the 12-week period. Follow-up testing will occur at Weeks 13 and 24.

**Discussion:**

This lifestyle intervention has the potential to provide a unique, non-surgical management option for people with LSS. Through decreased fat mass and increased function, we may reduce risk for obesity, chronic diseases of inactivity, and pain. The use of e-health interventions provides an opportunity for patients to become more involved in managing their own health. Behaviour changes including increased physical activity, and improved dietary habits promote overall health and quality of life, and may decrease future health care needs in this population.

**Trial registration:**

Clinicaltrials.gov, NCT01902979

## Background

Lumbar spinal stenosis (LSS) is a degenerative condition which typically affects adults in their sixth and seventh decades of life [1]. The estimated prevalence of symptomatic LSS ranges between 8.4% [2] and 9.3% in the general population, [3] and is on the rise worldwide [4]. There are an estimated 1.2 million people in the US with symptomatic LSS at any given point in time [2].

LSS is characterized anatomically by a narrow spinal canal and/or narrow nerve root foramina, resulting from degenerative changes in the spine. The most specific symptom of LSS is neurogenic claudication, which includes pain, numbness and weakness in the low back, buttocks and legs brought on by standing and exacerbated by walking [5]. Because of these symptoms, people with LSS avoid walking and exhibit sedentary behaviour [6]. Therefore, not only is LSS painful and debilitating, it also has a considerable impact on risk for chronic diseases of inactivity.

Sedentary behaviour has important implications for overall health in the LSS population [7,8]. Physical inactivity and accompanying weight gain increase the risk of many chronic diseases, notably obesity, metabolic syndrome, coronary heart disease, type 2 diabetes, and certain cancers [9-22]. A growing body of literature also supports a link between obesity-related systemic inflammation and musculoskeletal pain [15-19,21,22]. In particular, relationships have been established between low back pain and both fat mass, [23] and body mass index (BMI) [24-30]. Specific to physical activity, a recent study identified BMI as the strongest predictor of day to day function in people with LSS [31]. BMI was a stronger predictor of function than both disease severity and pain. This suggests that by targeting weight as a modifiable factor in people with lumbar spinal stenosis, we may also impact function. It is possible that by decreasing fat mass and increasing physical activity, we can reduce systemic inflammation and decrease the risk of obesity-related diseases, including pain, in people with LSS.

Despite the potential implications of weight gain and inactivity in LSS, to our knowledge there has been no research to date examining non-surgical options for weight management in overweight and obese individuals with this condition. The present study aims to address this gap by evaluating a newly developed lifestyle intervention aimed at promoting weight loss in LSS through behaviour change techniques, pedometer-based physical activity promotion, and nutrition education. In keeping with recent trends in medicine, this program was developed using an e-health (online) platform. The use of e-health interventions provides an opportunity for patients to play an active part in management of their own health, in co-operation with healthcare providers. This intervention has the potential to provide a unique, non-surgical management option for people with LSS, decreasing the risk for obesity, chronic diseases of inactivity, and musculoskeletal pain through decreased fat mass and increased physical activity.

### Objective

The objective of this study is to evaluate an e-health lifestyle intervention aimed at increasing physical activity, decreasing fat mass, and increasing quality of life in overweight and obese people with LSS. The main components of this intervention consist of pedometer-based physical activity promotion and nutrition education.

## Methods/Design

The project consists of three phases. Details regarding Phases 1 (program development) and 2 (intervention pilot) have been submitted in a separate publication and will not be presented here.

### Phase 1, development (Complete)

Develop the online (e-health) intervention tool used to deliver weekly personalized pedometer step goals and tips, as well as nutrition education sessions.

### Phase 2, intervention pilot (Complete)

Over the past 2 years, the Spinal Stenosis Pedometer and Nutrition Lifestyle Intervention (SSPANLI) was developed and piloted with 10 overweight and obese individuals with LSS. This pilot data was used to evaluate the efficacy, content and feasibility of the intervention. Based on feedback obtained during post-pilot interviews, the intervention was shown to be feasible and attractive to participants. Statistically significant improvements were observed for fat mass (dual x-ray absorptiometry: DXA), trunk fat mass (DXA), physical function (accelerometry), symptom severity (Swiss Symptom Severity Scale), caloric intake (DA plus 10.0), and mental health (SF-36). Publication of the pilot data is forthcoming.

### Phase 3

The final phase in this project, described here, is a fully powered randomized controlled trial comparing the Spinal Stenosis Pedometer and Nutrition Lifestyle Intervention (SSPANLI) to usual care for lumbar spinal stenosis. Recruitment for the trial began in August 2013. Ethics approval for the trial was obtained through the Conjoint Health Research Ethics Board of the University of Calgary.

### Study design and overview

The Spinal Stenosis Pedometer and Nutrition Lifestyle Intervention (SSPANLI) is a single-blind RCT comparing the SSPANLI intervention to usual non-surgical care for LSS. This project will evaluate the new e-health lifestyle intervention aimed at decreasing fat mass, increasing physical activity and improving quality of life in older adults with LSS who are overweight or obese. The SSPANLI protocol includes individualized pedometer-based activity recommendations and online nutrition education tools, as well as two personalized consultations with a Registered Dietitian and exercise specialist. Figure 1 presents a flowchart for the study.

**Figure 1 F1:**
[figure not shown]
Study flowchart.

#### Inclusion and exclusion criteria

All participants will be at least 45 years of age and will have received a diagnosis of LSS by a spine surgeon who has both examined the patient and reviewed imaging results (magnetic resonance imaging or computed tomography). All participants will be required to have a BMI of 25 kg/m^2^ or greater (overweight) and to have maintained a stable bodyweight for the previous 3 months. Exclusion criteria include diagnosed eating disorders, pregnancy, weight over 350 lbs, or any co-morbid conditions that would limit walking significantly or make participation in a walking program medically inadvisable, including severe arthritis, neuropathy or other neuromuscular disease, angina, cardiovascular disease, pulmonary disease, stroke or other neurological disorder, or peripheral vascular disease. Participants currently participating in a diet or lifestyle intervention for weight loss, who are on medications or herbal preparations known to influence bodyweight (including, but not limited to antidepressants and orlistate), or who have had changes in their prescription of lipid-lowering or diabetes medications over the past 3 months will be excluded.

#### Recruitment

All participants will be recruited through the University of Calgary Spine Program and Caleo Health. Spine patients are referred to Caleo Health Centre for a complete spine assessment to determine the most appropriate treatment (referral to a surgeon, physical medicine, physiotherapy, combination therapy etc.). It is through this triage process that the research nurse will be able to identify potential participants and contact them for possible participation in the trial. Spine surgeons from the University of Calgary Spine Program will also be made aware of this protocol, so that that their patient populations can be reviewed for potential inclusion. In the triage process, a review of the medical history including height and weight will be obtained (used to determine BMI). This information will be documented on both a triage form as well as documentation provided to the referring doctor. This information will be reviewed by the research nurse (who currently reviews all triage forms). Potential patients will either be contacted by phone or seen the day of the clinic visit to discuss the study. A screening form will be used to identify potential participants based on inclusion/exclusion criteria.

### Blinding and randomization

After completing the screening process participants will be randomly assigned to either the intervention group (n = 53) or the control group (n = 53). A computer-generated randomization sequence produced using R statistical analysis program will be used. Participants will be allocated to the group by the Study Coordinator, and will be aware of the allocated group. Those assigned to the control group will be offered the opportunity to try the intervention once the study is complete. All study investigators including the statistician, and research staff collecting data will be blinded to group allocation (single blind design). Participants will be asked not to comment to assessors regarding allocation.

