### Testing schedule

Following enrollment, patients will begin the study protocol, which involves 7 testing appointments over a 6 month period. These appointments include Baseline Visit 1 (week -1), Baseline Visit 2 (week 1), 6-week check-in (week 6), Follow-up Visits 1 and 2 (week 13) and Follow-up Visits 3 and 4 (week 24). The intervention begins at Baseline Visit 2 and runs for 12 weeks (weeks 1–12). Enrollment will be continuous throughout the study. Once patients are enrolled they will begin assessments at the next available scheduled date for Baseline Visit 1. Six-week check-in sessions will be arranged individually for each participant. The primary outcomes at each time point will be fat mass (%), steps/day, and quality of life (SF-36).

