#### 7-day activity monitoring

Participants will be provided with an activity monitor (Actigraph GT3X, Actigraph LLC, Pensacola, FL.) and an activity log. Participants will be instructed to wear the monitor during the waking hours, except when in contact with water. Participants will also be instructed how to complete a daily log to accompany the activity monitor. Participants will be asked to wear the monitor for the 7 days following Baseline Visit 1, to establish baseline activity level (steps per day). The activity monitor can provide an objective record of frequency, intensity, and duration of physical activity with minimal burden on participants. The Actigraph is widely accepted in the field as a valid and reliable means of assessing ambulatory physical activity [32-36].

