#### 3-day food records

Food and beverage intake will be assessed using 3-day food records. Participants will be trained on how to complete a 3-day food record by a Registered Dietitian on their first visit. Participants will then be asked to estimate portion sizes and record all food and beverages consumed for 2 weekdays and 1 weekend day. The food record will be completed in the week following Baseline Visit 1, to establish baseline dietary intake. Dietary intakes will be analyzed with Diet Analysis Plus 10.0 software (Thomson Wadsworth, Toronto, ON).

Participants will be provided with a self-addressed, stamped envelope to return the activity monitor, activity log, and 3-day food record to Mount Royal University.

### Baseline visit 2

Baseline testing during Baseline Visit 2 will include questionnaire completion, a Self-Paced Walking Test, balance testing, a neurological examination, and peak VO_2_ exercise test on a cycle ergometer. Intervention components of Baseline Visit 2 will include a one hour personalized consultation session with a Registered Dietitian, and a one hour personalized physical activity counseling session with an Exercise Physiologist (including instructions regarding how to use the pedometer). Participants will also be guided through the process of initial login and navigation of the e-health intervention website, as well as provided with instructions regarding how to fill out the daily personal log book.

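### As written, allocation known to participants precedes collection of baseline steps, diet and SF-36, which can bias change from baseline in either direction

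*Protocol article*

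**What the plan says.** The Recruitment section describes screening as an eligibility check on paper: "A screening form will be used to identify potential participants based on inclusion/exclusion criteria". Blinding and randomization then states "After completing the screening process participants will be randomly assigned", and adds "Participants will be allocated to the group by the Study Coordinator, and will be aware of the allocated group". Assessors, investigators and the statistician are blinded; participants are not.

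Testing schedule puts baseline testing after enrollment: "Once patients are enrolled they will begin assessments at the next available scheduled date for Baseline Visit 1". The baseline measures follow in this order:

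- **Fat mass:** DXA at Baseline Visit 1.
- **Steps:** "Participants will be asked to wear the monitor for the 7 days following Baseline Visit 1, to establish baseline activity level (steps per day".
- **Diet:** "The food record will be completed in the week following Baseline Visit 1, to establish baseline dietary intake".
- **SF-36:** part of the questionnaire at Baseline Visit 2, completed on the intervention website. The same visit holds the first counselling sessions, and the intervention starts there.

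The Intervention website training section uses the baseline step count to set each participant's weekly goals. The Statistical analysis section compares change from baseline to 13 and to 24 weeks between arms for steps/day, fat mass (%) and SF-36. The Sample size estimate section names steps as the main outcome.

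**The concern.** Steps are behaviour, and the SF-36 and food record are self-reports. Someone who knows they are entering a walking and diet programme may start early, or may record a week that leaves room to improve. Someone who knows they are a control has neither reason. Blinded assessors do not help, because the person who can react is the participant.

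The between-group test is on change, so a baseline difference caused by knowing the arm enters the estimate directly. It also feeds the step goals, so it can alter the intervention itself. It cannot be fully repaired in analysis, because a baseline recorded with the arm known cannot be collected again.

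**Working it through.** **1. Order of events in the text.** Form-based screening (Recruitment), then random assignment with participants aware of their arm (Blinding and randomization), then Baseline Visit 1 at the next available date (Testing schedule), then the week of step and food recording, then Baseline Visit 2 with the SF-36. No section places a baseline test before randomization, and none withholds the allocation until baseline is complete. Nor does any section give the moment of disclosure.

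**2. The plan's own figure.** Inputs from Sample size estimate: difference 750 steps, SD of the difference (5000 − 0)/4 = 1250, two-sided α = 0.05, power 80%.

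n = 2(1.96 + 0.84)² / (750/1250)² = 15.68 / 0.36 = 43.56, rounded up to 44 per group. The stated 44 is reproduced. Power at 44 per group is 80.4% (normal approximation).

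**3. How a baseline shift enters.** Let b be the amount by which knowing the arm raises mean baseline steps in the intervention arm relative to control, and let δ be the true difference in change. With follow-up values held fixed, the expected difference in unadjusted change is δ − b. The article specifies no baseline adjustment, so the shift passes through one for one.

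**4. Illustration.** The documents give no value for b. I assume 75, 150 and 250 steps/day, which are 10%, 20% and 33% of 750. The standard error is 1250 × √(2/44) = 266.5.

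- Power if the intervention baseline rises: Φ((750 − b)/266.5 − 1.96).
- Type I error if it falls by the same amount, with no true effect: P(|Z + b/266.5| > 1.96).

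| Assumed shift (steps/day) | Apparent effect if baseline rises | Power | Type I error if baseline falls |
|---|---|---|---|
| 0 | 750 | 80% | 5.0% |
| 75 | 675 | 72% | 5.9% |
| 150 | 600 | 62% | 8.7% |
| 250 | 500 | 47% | 15.5% |

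For the SF-36 the article gives no SD or target difference, so no comparable figure can be worked out.

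**The case against.** The strongest reply is that the timing is partly inferred. A reader might take the article to say that participants are told their arm straight after screening and before any baseline test. It does not say that: it gives no moment of disclosure, Testing schedule does not mention randomization, and the study flowchart, where the sequence would normally appear, is not shown. If allocation is in practice held back, the sponsor need only say so. What stands is that the written order points one way and nothing in the text prevents early disclosure.

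A reader might also infer that all three primary outcomes are compromised. The documents do not support that. Fat mass is an objective DXA measurement at Baseline Visit 1 and knowledge of the arm should hardly move it. During the baseline week participants have no pedometer, step goal or counselling, and any reaction to wearing the monitor itself occurs in both arms. Only the differential part matters.

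A third tempting step is a firm size for the damage. Dividing 750 steps by the 20% goal suggests a baseline of 3,750 steps/day, and a 5–10% reaction would then remove 188–375 of the 750 steps. But 3,750 is not in the documents, the 750 derives from the pilot's encouragement schedule while the 20% is the trial's own goal, and the 5–10% is a guess. It also shows only a bias against the intervention, when the opposite is equally possible. Nor does the text give evidence that disappointed controls would leave before Baseline Visit 1; they are offered the intervention afterwards.

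**Conclusion.** The concern holds as a risk created by the written sequence, not as a demonstrated bias. Steps/day and SF-36, and diet as a secondary outcome, can be measured at baseline in participants who know their arm. The effect on the between-group change can go either way, and its size is unknown.

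The figures of 72–47% power and 5.9–15.5% type I error rest on assumed shifts of 75–250 steps/day, the plan's SD of 1250, 44 evaluable participants per group and an unadjusted comparison of change. They show that a shift well below the target effect would matter. They do not predict what will happen.

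An amendment is justified because steps are the outcome on which the trial was sized and prevention is cheap.

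**What to change.** Amend Blinding and randomization so that allocation is made, or at least revealed, only when the following are complete: Baseline Visit 1, the 7-day monitoring, the food record, and all Baseline Visit 2 testing including the questionnaire. The reveal then comes immediately before the counselling components, handled by the Study Coordinator away from the blinded assessors. Because the questionnaire sits on the intervention website, it should be reachable without opening the intervention content.

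Nothing in the schedule requires earlier allocation: "The intervention begins at Baseline Visit 2 and runs for 12 weeks (weeks 1–12". The counselling already draws on the baseline food record and step count, so both must be in hand by then. No visit is added. The costs are that the dietitian and exercise physiologist must be booked before the arm is known, some of that time going unused for controls, and that the reveal must be kept from assessors on site.

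Recruitment began in August 2013, so some participants may already have followed the present order. Flag them, and add a sensitivity analysis comparing follow-up values between arms without subtracting baseline. This avoids the affected measurement, though it may be less precise than an analysis of change, and it does not undo any effect of a shifted baseline on the step goals. If allocation is already withheld until baseline is complete, one sentence stating so resolves the point.

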### Testing schedule

Following enrollment, patients will begin the study protocol, which involves 7 testing appointments over a 6 month period. These appointments include Baseline Visit 1 (week -1), Baseline Visit 2 (week 1), 6-week check-in (week 6), Follow-up Visits 1 and 2 (week 13) and Follow-up Visits 3 and 4 (week 24). The intervention begins at Baseline Visit 2 and runs for 12 weeks (weeks 1–12). Enrollment will be continuous throughout the study. Once patients are enrolled they will begin assessments at the next available scheduled date for Baseline Visit 1. Six-week check-in sessions will be arranged individually for each participant. The primary outcomes at each time point will be fat mass (%), steps/day, and quality of life (SF-36).

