### Sample size estimate

Pilot study data was used to power the planned RCT. The pilot study provided an estimate of the variability in the number of steps taken for 10 participants with LSS. We used a crude estimate of the sample standard deviation for steps in place of the unknown population standard deviation. Our main study outcome is number of steps at the end of the 12-week intervention. For the pilot study, an average increase of 375 steps was encouraged during each six-week period. At the end of the study, an average increase of 750 steps was anticipated. This was used to judge whether the intervention was effective. With α = 0.05 and a mean difference of 750 steps at the end of study, the standard deviation of the difference was calculated as follows:

$$\mathrm{Std}.\mathrm{Dev}\;\mathrm{of}\;\mathrm{diff}=\tilde{\sigma }=\frac{\left(L-S\right)}{4}=\frac{\left(5000-0\right)}{4}=1250$$

L equals largest and S equals smallest anticipated difference in the number of steps from baseline to follow-up period.

The formula for the sample size required, per group, (with α = 0.05, the probability of type I error, 80% power and an effect size of 0.6) to compare two population means, *μ*_1_ and *μ*_2_ with common variance, *σ*^2^, is

$$n\;=\;\frac{2{\left(Z_{1-\alpha /2}+Z_{1-\beta }\right)}^{2}}{{\left(\frac{\mu_{1}-\mu_{2}}{\sigma }\right)}^{2}}=\;\frac{2{\left(1.96+0.84\right)}^{2}}{{\left(\frac{750}{1250}\right)}^{2}}=43.60\approx 44$$

We concluded that a sample size of 44 people per group would be needed to detect a between-group difference of number of steps taken from baseline to week twelve. Based on the dropout rate for the pilot, we anticipate a potential dropout rate of 20% for the RCT. We will therefore aim to recruit 106 participants (53 per group). This number has been deemed feasible based on the volume of lumbar spinal stenosis patients seen through the University of Calgary Spine Program (approximately 500 per year).

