### Statistical analysis

Using the raw quantitative data from the participants of both groups we will present descriptive statistics summarizing the mean and standard deviation with respect to all the primary study variables. Age and sex distributions of the participants will be tabulated. Our goal is to establish reliable point estimates of the study variables and to characterize the variability within the two groups.

The independent variable will be the intervention, while the dependent variables will include steps/day, fat mass (%) and health related quality of life (SF-36 overall score). Linear mixed-effects models will be used to determine whether the changes for each time period (baseline to 13 weeks, baseline to 24 weeks) were significantly different between intervention and control groups. Repeated measures analysis of variance (RANOVA) will be used to examine within group changes from baseline to 13 weeks and from baseline to 24 weeks.

We will also examine changes in the following variables: Biochemical markers of obesity and associated co-morbidities including Plasma glucose, Serum adipokines (c-reactive protein (CRP), leptin, IL-1β, IL-6, IL-8, TNF-α, MCP-1 and insulin), and Serum lipids (total cholesterol, LDL cholesterol, HDL cholesterol and triglycerides); Physical function (Physical Function Scale of Swiss Spinal Stenosis Questionnaire); Walking capacity (Self-Paced Walking Test distance); Balance (mean deviation from centre of pressure from balance platform); Neurological impairment (Neurological Impairment Score); Pain (Symptom Severity Scale and visual analog scales); Back pain related disability (Oswestry Disability Index); Fear of movement (Tampa Scale for Kinesiophobia); Depression (CES-D total score); kilocalorie intake (kcal/day); Fat intake (grams/day); Vegetable and fruit intake (Canada Food Guide servings/day); Fibre intake (grams/day); and Change questions for activity, mood, overall health, calories, vegetable intake, and fibre intake. Clinical MRIs we will be used to assess whether imaging findings are predictive of change in the primary outcome variables following the intervention.

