When an inferential test is performed, the level of significance, α will be set at 0.05, and results will be presented with p-values. In all tests, p-values less than 5% (< 0.05) will be considered statistically significant. All quantitative analyses and hypothesis will be performed using Minitab software, version 16 ^5^ and R programming language, version 2.15.1. Specifically, we will use the *gee* package, *pwr* package and *samplesize* package downloaded from the Comprehensive R Archive Network (CRAN) repository for our power and sample size calculations.

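### Three primary outcomes at two time points, unranked and each tested at 0.05, conflict with the single main outcome on which the sample size rests

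*Protocol article*

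**What the plan says.** Four statements in the Protocol article bear on this point.

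- **Testing schedule** declares three primaries, repeated over time: "The primary outcomes at each time point will be fat mass (%), steps/day, and quality of life (SF-36".
- **Statistical analysis** lists the same three without ranking them: "the dependent variables will include steps/day, fat mass (%) and health related quality of life (SF-36 overall score". Mixed-effects models then ask whether "changes for each time period (baseline to 13 weeks, baseline to 24 weeks) were significantly different between intervention and control groups".
- **Statistical analysis** also sets the threshold: "In all tests, p-values less than 5% (< 0.05) will be considered statistically significant".
- **Sample size estimate** names one outcome at one time: "Our main study outcome is number of steps at the end of the 12-week intervention". The calculation follows from that single outcome: "With α = 0.05 and a mean difference of 750 steps at the end of study", "80% power and an effect size of 0.6", and "We concluded that a sample size of 44 people per group would be needed".

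No section gives a testing order, an alpha split, a rule that all primaries must succeed, or a multiplicity adjustment. No section explains how one main outcome and three primary outcomes fit together.

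**The concern.** The protocol gives two different answers to the question of which result decides the trial. By the sample size section, it is steps at the end of the intervention. By the testing schedule and the analysis section, it is three outcomes at two follow-ups, all of equal standing and all judged at 0.05.

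This matters most if the results are mixed. Suppose steps/day shows no difference at week 13 but fat mass reaches p = 0.04 at week 24. One section would support reporting a positive primary result, and another would support reporting that the main outcome failed. A choice made after the data are seen would not carry a 5% error rate. The sample size is also tied to one test at 0.05, so it cannot be carried over to a family of six without a stated rule.

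**Working it through.** **1. Reproduce the plan's figure.** Inputs from Sample size estimate: difference 750 steps, SD 1250, two-sided alpha 0.05, 80% power.

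n per group = 2 × (1.96 + 0.84)² / (750/1250)² = 2 × 7.84 / 0.36 = 43.56. With unrounded normal quantiles it is 43.60, the printed value. Both round up to 44, so the figure reproduces. It holds for one test at 0.05.

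**2. Count the primary between-group tests.** Three outcomes (Testing schedule) × two periods, baseline to 13 weeks and baseline to 24 weeks (Statistical analysis) = 6. The within-group repeated-measures tests are not counted.

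**3. Family-wise error if a significant result on any one test is taken as a positive primary result.** All values are under the global null.

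- Six independent tests: 1 − 0.95⁶ = 0.265.
- Week 13 only, three independent tests: 1 − 0.95³ = 0.143.

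**4. Allow for correlation.** The document gives no correlations, so these are assumptions. The week-13 and week-24 changes share a baseline. With equal variances and equal between-visit correlations, that alone makes the two changes correlate at 0.5, so 0.5–0.9 is a reasonable range for time. Outcomes are taken to correlate at 0–0.5. The results come from simulating six two-sided z-tests (at least 1,000,000 draws per cell), with the correlation matrix built as outcomes × time points:

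| Correlation between time points | Outcomes 0 | Outcomes 0.3 | Outcomes 0.5 |
|---|---|---|---|
| 0.5 | 24.8% | 23.8% | 22.0% |
| 0.7 | 23.0% | 22.0% | 20.3% |
| 0.9 | 19.7% | 18.7% | 17.3% |

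For week 13 alone (three tests), the error is 14.3% with uncorrelated outcomes and about 12.5% with outcomes correlated at 0.5.

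**5. What the two obvious remedies would cost.** A single primary (steps, week 13) keeps alpha at 0.05 and n at 44. Bonferroni on the steps calculation would do the following:

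| Rule | Alpha per test | n per group for 80% power, before dropout | Power at 44 per group |
|---|---|---|---|
| One test | 0.05 | 44 | 80% |
| Three tests | 0.0167 | 59 | 66% |
| Six tests | 0.0083 | 68 | 57% |

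**The case against.** The strongest reply is that no success rule is stated. The sections list outcomes, comparisons and a significance threshold. None says that one significant result out of six makes the trial positive. A reader might infer that rule, or infer that week-24 fat mass alone would count as success under the plan, but neither is written. If the sample size section is taken as governing, the error rate for the main claim is 5%. This part of the objection stands, and it makes every error rate above conditional.

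It can also be said that multiplicity detail is commonly left to an analysis plan or full protocol, and neither is shown. That is fair for the procedure. It does not dispose of the point, because the conflict over what is primary is in the text shown, and so is the blanket 0.05. Adjusted p-values could still be judged against 0.05, but nothing in the article says that they will be.

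Two further inferences are tempting and should not be made.

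- **Secondary variables.** One might count the long list of other variables at both visits and predict a number of false positives. The protocol says only that changes in them will be examined, and it applies the 0.05 level when an inferential test is performed. It does not commit to a between-group test of each variable at each visit.
- **Power.** One might say that the trial is adequately powered for only one of the six tests. The document gives no target difference or SD for fat mass or SF-36, so power for those is unknown, not shown to be low.

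Finally, the Objective section presents activity, fat mass and quality of life as parallel aims. Demoting two of them is a real change to the trial's emphasis, and that cost should be acknowledged.

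**Conclusion.** The point holds as an inconsistency that must be resolved. The protocol declares three unranked primary outcomes at two time points, sets 0.05 for all tests, and elsewhere names and powers one main outcome at one time point.

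The size is conditional. If a significant result on any of the six tests were reported as a positive primary result, which the text neither states nor prevents, the family-wise error under the global null would be 26.5% with independent tests. It would be about 17–25% with assumed correlations of 0.5–0.9 between time points and 0–0.5 between outcomes. Restricted to week 13 it would be about 12.5–14%. All of these exceed 5%, so the conclusion does not depend on the exact correlations. It does depend on the any-one-of-six reading, and a flat claim that the trial's error rate is above 20% would go further than the text.

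**What to change.** Reconcile Testing schedule, Sample size estimate and both statements in Statistical analysis:

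- Name one primary outcome: the between-group difference in change in steps/day from baseline to week 13, tested at two-sided 0.05. This follows the protocol's own sample size section and leaves 44 per group as it is.
- Make fat mass (%), SF-36 and all week-24 comparisons secondary.
- If confirmatory claims are wanted for any of these, fix a testing order before unblinding, for example a fixed sequence after steps in which each test is made only if the one before it is significant at 0.05. The order is the sponsor's choice.
- Limit the statement on significance in all tests so that it agrees with that order.

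The cost is wording, with no extra participants or data. Recruitment began in August 2013, so the change should be recorded as a dated amendment. The Blinding and randomization section says that the investigators and the statistician are blinded to allocation, so this can be done credibly before unblinding. The downside is that fat mass and SF-36 lose stand-alone primary status and, under a fixed sequence placed after steps, could be claimed only if steps succeeds. If the sponsor prefers to keep several primaries, an alpha split is possible, but a Bonferroni split would lower power for steps at 44 per group to 66% (three tests) or 57% (six tests).
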